## Abstract

**Background:**

Environmental exposure, including green-blue space and walkability, may influence mental health through various physiological pathways. Traditional methods have limitations in capturing dynamic environmental exposure effects on mental health.

**Objective:**

This study aims to investigate the associations between minute-level environmental exposure and stress-related biomarkers using GPS-based measurements and wrist-worn biosensors in an urban population.

**Methods:**

In this prospective observational study, we will recruit 750 participants (aged 18-80 years) in Hong Kong from September 2024 to December 2026. This includes a pilot study supported by internal funds starting in September 2024 and external funding from the Health and Medical Research Fund by the Hong Kong Health Bureau in July 2025. Participants will undergo a 1-week experiment wearing biosensors and carrying GPS devices while completing daily surveys and entry and exit questionnaires. Primary outcomes include digital biomarkers (electrodermal activity, blood volume pulse, and skin temperature) from wrist-worn sensors and associations with the environmental exposures of air pollution, urban density, and green-blue space access. Secondary outcomes comprise questionnaire responses, physical activity metrics from accelerometer data, and environmental exposure assessments, including mobility barriers, land use mix, road accessibility, and thermal conditions. Focus groups will be conducted to refine study protocol and assess device-wearing experience.

**Results:**

The study received ethical approval from the Human Ethic Research Committee (award numbers: EA240125 and EA240514). As of June 30, 2025, a total of 150 participants completed the pilot study (September 2024 onwards), achieving a 94% (141/150) completion rate with strong device compliance (141/150, 94% valid biosensor days; 137/150, 91% daily questionnaires). Protocol refinements based on participant feedback were implemented without altering core instruments. The main study supported by the Health and Medical Research Fund, commenced in July 2025, with 30 participants enrolled as of September 2025. Data collection for 750 participants will continue until December 2026. We are at an early stage of data cleaning and preprocessing for the pilot study. Data analysis is expected to be completed by June 2027, with results anticipated to be published in 2027 and 2028.

**Conclusions:**

This study’s innovative integration of continuous environmental monitoring and stress-related biomarker may provide new insights into environment–health relationships. Findings will inform public health initiatives for mental well-being promotion and urban planning interventions.

**International Registered Report Identifier (IRRID):**

DERR1-10.2196/84919

## Introduction

The World Health Organization reported that more than one billion people worldwide experience mental health issues affecting daily lives [1]. High-rise residential buildings, particularly clustered in Hong Kong, were reported to increase the burdens of an already stressful life and threaten the well-being of residents living on the upper floors [2]. Population health surveillance data from the Hong Kong Department of Health for the years 2020 to 2022 indicated that approximately 1.2% of the surveyed population had been diagnosed with depression, while 0.9% of the respondents reported anxiety [3]. These rates were double the numbers reported from 2014 to 2015. Based on this, depression and anxiety are recognized as the most common mental health issues in Hong Kong. Furthermore, the prevalence of severe depression among Hong Kong residents increased by more than 30% between 2020 and 2023 [3]. Mental health problems present a younger trend, as a territory-wide study in 2015 showed 11.3% of children and adolescents in Hong Kong experienced common mental disorders [4]. A separate study reported an increased prevalence of 16.6% between 2019 and 2022, during social unrest and the COVID-19 pandemic [5]. However, very few people are likely to seek professional help. It has been estimated that 74% of mental health sufferers do not seek any form of professional assistance in Hong Kong [4].

Prior research has reported that the status of mental health is associated with genetic factors and wider social determinants encompassing the life span [6,7]. These determinants include socioeconomic conditions, intergenerational relations, living community social and built environment, and the affordability and accessibility of medical care [8,9]. The environment shapes many aspects of daily life. Evidence shows embracing the natural environment, especially exposure to green and blue space, contributes to improving human health [10,11]. However, existing research about environmental exposure related to the status of mental health usually focuses on the residential neighborhoods, leading to a “stationary bias” [12], while dynamic exposure assessments that concentrate on people’s mobility patterns (ie, changes in locations over time) [13] are essential to estimating total environmental exposures [14].

Traditional measurement using questionnaire surveys has been found time- and labor-consuming [15,16], and self-reported instruments are subject to individual characteristics and preferences [17,18]. Recent studies have increasingly adopted wearable devices, allowing for continuous monitoring of physiological parameters and real-time assessment of physical and mental health conditions [19-22].

In this study, we aim to investigate the association between changes in environmental exposure, including green and blue space and walkability, and changes in biomarkers associated with mental health by using minute-level GPS-based environmental measurements and wrist-worn biosensors (Figure 1). Primary analyses will examine associations between 3 environmental exposures (air pollution, urban density, and green-blue space access) and 3 digital biomarkers (electrodermal activity, pulse rate, and skin temperature). Secondary analyses will investigate physical activity metrics and explore questionnaire responses and additional environmental assessments, including walkability, mobility barriers, land use mix, road accessibility, and thermal conditions.

**Figure 1 figure1:**
[figure not shown]
Conceptual framework of the study. GIS: geographic information system; NDVI: normalized difference vegetation index; MET: metabolic equivalent of task.

We hypothesize that environmental exposure–biomarker relationships exhibit spatial and temporal heterogeneity across activity space, characterized by both acute physiological responses and cumulative effects. Physical activities and daily behavior are expected to mediate these relationships, through activity types and intensities. Moreover, we propose that the stress responses to environmental features will demonstrate individual-specific patterns, reflecting the complex interaction between personal characteristics and environmental factors. This protocol addresses current methodological gaps by implementing dynamic geospatial exposure assessment combined with continuous monitoring of digital biomarkers.

## Methods

### Study Design and Objectives

This study adopts a mixed methods longitudinal design to investigate the pathways through which environmental exposures influence mental health by physical activity mechanisms in Hong Kong adults.

Primary outcomes include digital biomarkers (electrodermal activity, pulse rate, and skin temperature) from wrist-worn sensors and their associations with the 3 environmental exposures of air pollution, urban density, and green-blue space access. Secondary outcomes comprise questionnaire responses, physical activity metrics from accelerometer data, and environmental exposure assessments, including mobility barriers, land use mix, road accessibility, and thermal conditions.

To address concerns regarding multiple testing, we will report the primary associations between environmental exposures and biomarkers defined above with α=.01 to minimize false positives (3 primary outcomes × 3 primary exposure measures = 9 comparisons). For secondary comparisons, we set α=.05, recognizing that this may include some false positives. However, these are exploratory analyses, and significant associations would be interpreted as suggestive to be examined with further study.

### Participants’ Recruitment

This study adopts a mixed methods approach, combining quantitative and qualitative methods with a cross-disciplinary approach. For sampling strategy, we apply a predefined approach by integrating stratified random sampling with multistage sampling methodologies. Initially, we categorize small territorial planning units (STPUs) in Hong Kong based on two indicators: (1) percentage of older adults (aged ≥65 years) using Hong Kong Census data: this serves as a proxy for age-specific demographic composition in each STPU, indicating areas with aging population densities and their corresponding service demands (eg, health care facilities and community support infrastructure) [23]; and (2) proximity to the nearest green space using OpenStreetMap: this indicator calculates the walking time from an STPU centroid to the nearest urban or country park, representing a crucial environmental factor for physical activities and recreation across all age groups. We further categorize STPUs into low, median, and high groups using terciles for each indicator: (1) Percentage of older adults: low (3.58%-15.78%), medium (15.78%-20.79%), and high (20.79%-65.76%); and (2) proximity to nearest park: low (8.72-56.00 minutes), medium (3.86-8.71 minutes), and high (0.10-3.85 minutes). Finally, we select STPUs based on indicator combination (percentage of older adults–proximity to green space in minutes): high–high (n=32), high–low (n=14), low–high (n=11), and low–low (n=40).

The target sample size of 750 is based on the current Hong Kong population size of 7.4 million. The sample size represents approximately 1 out of 10,000 of the population, which is a common patient representation in a mid-sized region [24,25].

The recruitment strategy includes community engagement through promotional materials in community centers and snowball recruitment through initial participants. Promotional materials include a QR code for participants to provide basic information (ie, contact, age, gender, and residential STPU). During enrollment, we perform prescreening and monitor recruitment rates across STPU strata weekly to ensure balanced distribution across demographics and geographic areas. To mitigate sampling bias toward healthier or smartphone-familiar adults, we have (1) increased targeted outreach in underrepresented areas, (2) provided device-wearing tutorials in multiple languages and formats to accommodate varying digital literacy levels, and (3) provided backup smartphones for participants without compatible devices.

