### Strengths and Limitations

This study has several strengths. First, the integration of minute-level GPS tracking with continuous biosensor monitoring represents a significant methodological advancement, allowing precise spatiotemporal assessment of environmental exposure and stress-related responses. Second, we are collecting data from diverse population groups, including older adults and foreign domestic workers, allowing us to compare demographic groups (eg, younger adults vs older adults) and explore differences in stress impact from physical-social-built environments. This diversity enhances the generalizability of our findings across different population segments in Hong Kong. Third, the combination of objective biomarkers, questionnaires, and GPS records provides a comprehensive assessment of the relationship between environmental exposure and mental health. Fourth, the extended monitoring period allows for examination of both acute and cumulative effects of environmental exposure, addressing a significant gap in existing literature. Lastly, this study design includes baseline measurements before environmental exposure, enabling accurate assessment of stress-related changes.

However, several limitations should be acknowledged. First, our exclusion criteria (no neuropsychological disorders, no severe mobility limitations, able to maintain device charging) may systematically exclude individuals at high mental health risk, who may be less likely to enroll in the study. This limits the generalizability of findings to the broader population with mental health concerns. Second, the study protocol cannot be applied for children and teenagers, who have become a major concern in the region regarding mental health problems. As teenagers and children require a guardian when conducting the experiment, different study protocols are suggested for future research. Third, participant reactivity to wearing monitoring devices may influence behavior and stress-related responses, although this effect typically diminishes over time. Lastly, this protocol is not designed as a randomized controlled trial, and therefore is not applicable for causal inference on environmental exposure.

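### The sample is labelled stratified random and multistage but recruited as volunteers in four contrasted strata, and its size rests on a population fraction that says nothing about precision

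*Protocol article*

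**What the plan says.** All but two of the statements below come from Participants' Recruitment in the protocol article.

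- **Label.** The sampling strategy is introduced with "we apply a predefined approach by integrating stratified random sampling with multistage sampling methodologies".
- **Strata.** STPUs are split into terciles on two indicators: the share of residents aged 65 or over, and walking time to the nearest park. Then: "Finally, we select STPUs based on indicator combination", namely "high–high (n=32), high–low (n=14), low–high (n=11), and low–low (n=40").
- **Size.** "The target sample size of 750 is based on the current Hong Kong population size of 7.4 million", followed by "The sample size represents approximately 1 out of 10,000 of the population, which is a common patient representation in a mid-sized region".
- **How people enter.** "The recruitment strategy includes community engagement through promotional materials in community centers and snowball recruitment through initial participants". The materials carry a QR code through which people supply contact details, age, gender and residential STPU. Prescreening and weekly monitoring by stratum are meant to keep enrolment balanced. Bias toward healthier or smartphone-familiar adults is acknowledged, with three mitigations.
- **Claim.** Strengths and Limitations, after describing the diverse groups enrolled, states: "This diversity enhances the generalizability of our findings across different population segments in Hong Kong". The limits it acknowledges are the exclusion criteria, the absence of children and teenagers, reactivity to the devices, and the non-randomized design.
- **Error rate.** Study Design and Objectives, and again Data Processing and Analysis, set α=.01 for nine primary exposure-biomarker associations.

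**The concern.** Random selection lets a reader generalize from sample to population by design, because selection probabilities are known. A sample of people who answered publicity or were referred by friends lacks that property, however well its strata are balanced. If the label stands, later papers will cite it, and estimates for motivated volunteers in contrasted districts may be read as estimates for Hong Kong adults.

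The second issue is the basis for 750. A sampling fraction sounds like a justification, but it does not tell the reader what size of association the study can detect at its chosen α. The article therefore gives no benchmark against which to judge whether 750, or a smaller number actually reached, is enough.

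**Working it through.** **1. Label against procedure.** Stratified random sampling needs a random draw within strata. Multistage sampling, if random, needs one at each stage. The article's stages, in order, are:

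- STPUs: chosen by indicator combination; no draw described.
- Households: not mentioned as a stage.
- Persons: self-registration from community-centre materials, or snowball referral.
- Enrolment: prescreening and monitoring for balance by stratum, district, gender and age group (Participants' Recruitment; Participant Eligibility).

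Monitoring volunteers against strata is quota control. It can balance the variables monitored but does not produce known selection probabilities.

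**2. Coverage.** Two indicators in terciles give 3 × 3 = 9 combinations. Those selected are high-high, high-low, low-high and low-low: 32 + 14 + 11 + 40 = 97 STPUs. The other 9 − 4 = 5 combinations, each with a medium tercile on at least one indicator, are not selected. The article does not make clear whether the 97 are all the STPUs in those four cells or the ones drawn from them.

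**3. The stated sample size.** 7,400,000 / 10,000 = 740, against 750 stated. In the other direction, 750 / 7,400,000 = 1.01 per 10,000. The article's arithmetic reproduces.

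**4. Does the fraction bear on precision?** Take the 95% half-width for a 50% proportion under simple random sampling, with the finite-population correction: 1.96 × √(0.25/750) × √((N − 750)/(N − 1)).

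| Population N | Half-width at n = 750 |
|---|---|
| 0.74 million | 3.58 points |
| 7.4 million | 3.58 points |
| 74 million | 3.58 points |

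Population size makes no practical difference. Conversely, the 1-in-10,000 rule would ask for 74 people in a population a tenth the size (half-width 11.4 points) and 7,400 in one ten times larger (1.1 points). Equal fractions give very unequal precision.

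**5. What a relevant statement would look like.** The article gives no effect size, SD, power or sidedness, so this is an illustration. Assume two-sided α=.01, 80% power and independent participants. By Fisher's z, the detectable between-person correlation is r = tanh((2.576 + 0.842)/√(n − 3)).

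- n = 750: tanh(3.418/√747) = .124
- n = 705, applying the pilot's 94% completion (0.94 × 750): tanh(3.418/√702) = .128

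These figures concern comparisons between people, such as weekly or cumulative exposure against a person's average biomarker level. Minute-level associations within a person draw on repeated measurements and have different precision, which these figures do not describe.

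**The case against.** Several points on the other side have weight.

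- **A condensed article may omit a random step.** A draw of STPUs could be set out in a fuller document. That would not repair the person stage, where publicity and referral are stated outright.
- **Contrasting strata is a legitimate choice.** Selecting high and low cells widens exposure contrast, and an association study does not need a representative sample. This stands. The fault lies in the label and the unqualified claim, not in the choice of cells.
- **Bias is acknowledged.** The article names sampling bias, lists mitigations, and limits generalizability on account of its exclusion criteria. Its strength claim is about diversity across population segments, not formal representativeness. So the claim needs qualifying, not deleting. Even so, neither volunteer and snowball recruitment nor the unsampled middle strata appear among the limitations.

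A reader might also infer that clustering is ignored and that standard errors are therefore too small. The article does not support that. Data Processing and Analysis plans random effects for individuals and does not exclude other levels, which an analysis plan could add. No intraclass correlation is given for STPUs. Exposures come from each person's own GPS track, so neighbours do not share one value, and much of the minute-level analysis is within person.

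Nor does it follow that a null result would be unreadable: a confidence interval can be interpreted without a detectable effect stated beforehand.

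**Conclusion.** The point holds in three parts. The sampling label is contradicted by the recruitment described directly after it. Coverage is limited to four of nine tercile combinations, and a generalizability claim is made without naming that limit or the volunteer route. The population-fraction rationale is arithmetically right (740 against 750) but irrelevant to power or precision at α=.01.

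The first two parts rest only on the text. The illustrative correlations of .124 and .128 rest on assumed two-sided testing, 80% power and independent participants, and the second also on 94% completion carrying over from the pilot. They do not show that 750 is too few. They show the kind of statement that is missing.

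The consequence is for what the study may conclude and for whom; nothing here invalidates the planned analyses. It should be corrected, and it is not a fatal flaw.

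**What to change.** 1. In Participants' Recruitment, replace the random and multistage label with a description of a quota-monitored volunteer sample within purposively contrasted STPU strata. State whether the 97 STPUs are all those in the four cells or a selection. If any random draw was made, describe it.
2. In Strengths and Limitations, qualify the generalizability claim, and add volunteer and snowball recruitment and the unsampled middle strata to the limitations.
3. Replace the 1-in-10,000 rationale with the detectable effect at the planned α, for 750 and for a realistic number of completers. State sidedness, power and the independence assumption, and say separately that within-person minute-level associations have different precision.
4. For between-person comparisons (daily, weekly and cumulative exposure), add a random intercept for residential STPU, at least as a sensitivity analysis.

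The cost is mostly wording. Residential STPU is already collected at registration, so item 4 needs no new data and one extra model term. The price is a weaker generalizability claim and, for between-person estimates, possibly slightly wider intervals. A term for referral chains is not asked for, because the article does not say that referral source is recorded.

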### Participant Eligibility

Study participants include adults aged 18-80 years, of any ethnicity or race, who possess a valid Hong Kong identity card and have been living locally for at least 6 months. This age range is selected to provide increased exposure variability while ensuring participants maintain sufficient mobility. Adults aged >80 years are not included because of potential mobility limitations.

To be eligible, participants must be able to walk without human assistance, travel to a study visit, have a mobile phone, read and write fluently in Mandarin, Cantonese, or English, provide informed consent and comply with the protocol, and be willing and able to complete all assessments. Ineligibility criteria include (1) pregnant or nursing, (2) neuropsychological disorders or neurological illnesses that affect understanding or compliance with study protocols, (3) medical conditions that significantly limit outdoor activities or daily mobility, (4) skin conditions that may be irritated by wearing sensors, (5) inability to maintain regular device charging routines, and (6) plans to travel outside Hong Kong during the 7-day study period, or (6) conditions that prevent smartphone use for daily questionnaires.

During the enrollment process, we perform prescreening on the residential location, gender, and age groups. The number of participants from each district and the proportions of different demographic characteristics (gender and age groups) will be regularly reviewed to ensure balanced distribution and avoid oversampling from specific groups or areas.

### Pilot Data Collection Protocol Adherence

We defined feasibility thresholds to assess protocol adherence. Study completion is defined as attending both study visits (preinterview and exit interview) and providing data during the 1-week experiment period without withdrawing. We set a threshold of ≥92% completion rate. Among participants who complete the study, we set secondary compliance thresholds: (1) ≥90% of participants provide ≥5 valid biosensor days (defined as ≥18 hours/day wear time); and (2) ≥90% of participants complete ≥5 of 7 daily questionnaires. Participants who complete study visits but fail to meet these minimum data requirements will be provided 1 additional week to collect data.

